### Enrollment and randomization procedure

To ensure a manageable workload for the LTCF nursing staff, the study will enroll only as many residents per team as the participating day shift RN deems to be reasonable. This number will be determined on an individual basis, and will constitute a contract between the research team and the LTCF RN.

Residents who have consented to participate will undergo a two-week delirium prevalence screening using the CAM and the DI (see assessments below) [37–39]. Residents who are delirium-free throughout this two-week period will be randomized for inclusion in the study. The number randomized per unit will be consistent with the number agreed upon by that specific unit nurse.

Residents will be randomized using an electronic data management (EDM) platform provided by the Information Management Services Unit (IMS) at McGill University/Lady Davis Institute of the Jewish General Hospital. IMS will employ simple random sampling, a basic sampling technique where a subset of individuals (a sample) is selected from within a larger set of individuals (a population). In such a method, each individual is chosen entirely by chance, and each member of the population has an equal chance of being included in the sample.

### The PREPARED Trial intervention

This PREPARED Trial intervention was developed by members of our team specifically for the LTC environment using an integrated knowledge translation strategy, which affirmed its feasibility in this setting [27]. The PREPARED Trial intervention is a multicomponent intervention (available in both English and French) consisting of the following:Decision Tree (Fig. 2): This one-page support tool is a 4-step algorithm designed to guide nursing decision-making.***Step 1*** consists of identifying residents at risk of developing delirium using the validated 5-item delirium risk screening tool [36]. For residents deemed at-risk, the tool will then guide the LTC nurse through the three following steps (below).***Step 2*** describes the application of a protocol designed to provide optimal stimulation, and is intended to be implemented by all LTC nursing staff members to all intervention arm participants. The stimulation protocol (STIMUL) involves three actions: 1) surveying the use of eyeglasses and hearing aids, the room lighting, and organization of the space; 2) orienting the resident to time (season, month, day) and to space (city, room); and 3) stimulating the resident with the help of familiar objects, photos, and life histories.***Step 3*** involves a set of specific nursing evaluations to assess the presence of the following five additional modifiable delirium risk factors (i.e., in addition to stimulation): 1) restraint use, 2) prolonged antipsychotic use, 3) dehydration, 4) vision problems, and 5) hearing problems) in preparation for the next step, which represents the specific PREPARED Trial intervention. Evidence of restraint and antipsychotic use are evaluated by examining the resident file, while dehydration is assessed via a thorough inspection of the skin and the mucous membrane of the mouth. Vision problems are evaluated using a tracking test, where residents are asked to follow the trajectory of a red ball within their field of vision. Hearing is assessed via a ‘finger rubbing’ test, where residents are asked to identify or react to sound, depending on their level of cognitive impairment.***Step 4*** describes six specific interventions aimed at reducing the impact of specific risk factors found to be present in Step 3. These six specific interventions are the core of the PREPARED Trial intervention, and are designed to reduce the impact of antipsychotic use, sensory impairment (vision and hearing), restraint use, and dehydration. They are:i.Antipsychotic Intervention (ANTIPSY): A letter signed by the study clinician team recommending a re-evaluation of the resident’s need for their antipsychotic medication as per clinical guidelines is inserted into the resident chart so that it may be read and signed by the treating physician.ii.Vision Intervention (AVSENS-VISION): A note is made in the resident chart, consultations with an optometrist are suggested, and a relevant intervention based on clinical judgement is suggested and/or implemented as needed.iii.Hearing Intervention (AVSENS-AUDIT): A note is made in the resident chart, consultations with an audiologist are suggested, and a relevant intervention based on clinical judgement is suggested and/or implemented as needed.iv.Restraint Intervention (CONTEN): All restraints are removed during care that requires the constant presence of a caregiver (nail care, feeding, and dressing changes).v.Hydration Intervention (HYDRA): A brightly colored container of fresh water is placed on the bedside table, the resident is offered liquids that s/he enjoys and at least one glass of liquid at each meal, 60-180 ml of liquid is offered during medication administration, and a glass of liquid is offered both after morning care and in the middle of the afternoon.vi.Hydration Intervention Plus (HYDRA++): For residents who are hesitant to drink, 60 ml of liquid is offered each time a caregiver enters the room in addition to the HYDRA protocol.

It is important to note that AVSENS-AUDIT represents a novel addition to the PREPARED Trial intervention. AVSENS, which stands for Auditory/Vision/Sensory, expands on the original VISION protocol as published by Voyer et al. (2014) to include both a visual *and* auditory evaluation/intervention [29]. This expansion was created to reflect the fact that hearing impairment (not just visual impairment) has been shown to be a risk factor for developing delirium in this population [21, 44, 45]. Furthermore, existing delirium prevention strategies have been shown to improve clinical outcomes by addressing hearing impairment [21].

In order to account for the possible effects of sensory impairment on cognitive testing [46–49], residents will be offered ‘Pocketalkers’™, or personal amplification devices, to use during trial assessments. Use of these auditory aids has been recommended as one of the strategies to avert the misdiagnosis or over-diagnosis of cognitive impairment in older adults with sensory impairment, and to improve the specificity of cognitive testing [50]. All personal amplification devices will be cleaned and sanitized with alcohol-based sanitation wipes prior to each use.

These six trial interventions will be integrated (where indicated) into the Therapeutic Nursing Plan (TNP) by the LTCF RNs who are mandated to carry out both the antipsychotic and the vision/hearing interventions. The restraint and hydration protocols, however, will be administered by LPNs and PSWs.2.Instruction Manual: This 3-page, easy-to read, manual provides detailed instructions on how to evaluate the 4 specific delirium risk factors. Specific content of each intervention is explained, and nursing directives are provided.3.Training Package: Provided by the research staff, the package includes (1): a tailored PowerPoint presentation to nurses (60 min) and LPNs/PSWs (30 min) covering all of the information needed to effectively use the PREPARED Trial intervention; and (2) delirium rounds on the unit during the follow up period (organized by the CRN, as needed) to discuss PREPARED Trial intervention-related issues. Training sessions for regulated staff members (i.e. RNs and LPNs) were accredited by Université Laval.4.Toolkit**:** This transparent box contains all of the necessary materials to evaluate risk factors (e.g., a red ball for the visual assessment protocol) and implement the interventions (e.g. voice amplifiers, magnifiers), as well as memory aid tools (poster, lanyard memory card, leaflet and notice board listing targeted residents). A box will be provided to each unit in the intervention arm of the study.

The intervention components are based on current best practices in LTC, and are not resource intensive – an important consideration in the context of budgetary constraints and reduced direct care time in this healthcare setting. This trial intervention has been shown to be both feasible and acceptable by Quebec LTC staff [29]. The intervention protocol is low-risk, non-invasive, and personalized to meet the risk profiles of each participant. Participants who no longer meet study inclusion criteria or who are no longer able to engage in the study and its protocols due to disease deterioration (as declared by the primary RN) will stop receiving the intervention and all study evaluations. Trial participants are free to withdraw from the study at any time.

### Adherence to the protocol and nursing staff satisfaction assessment

Adherence to the PREPARED Trial intervention (as documented by the addition of the intervention protocols to the TNP) in the intervention arm will be evaluated by the CRN. In addition, RAs will record the use of hearing/vision aids, and the presence of water and restraints (AVSENS-VISION, AVSENS-AUDIT, HYDRA, HYDRA++, and CONTEN) at every weekly face-to-face assessment with residents during the follow-up period. Nursing staff perceptions of the PREPARED Trial multicomponent intervention will be evaluated at study end using a questionnaire to assess intervention relevance, clarity, perceived burden, and sustainability [29].

### Blinding

LTCFs will not be blinded to group allocation (i.e. control/intervention), as trial arm allocation will obvious (the nursing staff in the intervention group will be trained prior to their participation and receive toolkits and reminder posters, while those in the control group will not). Similarly, the RAs tasked with conducting resident assessments will also not be blinded to group allocation, as they will be constantly exposed to the everyday workings of participating LTCFs. For example, certain visual cues (i.e. materials in the charting room) may indicate the trial status of many LTCFs. However, all research staff members responsible for abstracting information pertaining to modifiable delirium risk factors, medical consultations, and any LTCF transfers will be blinded to resident assessment scores, and should engage in such tasks with impartiality. The research team member administering the CAM/DI for a given resident will also be blinded to the cognitive level assessment of that resident. Finally, all researchers tasked with analyzing the data obtained from this study will be blinded to group allocation, as all LTCF names and randomization statuses will be automatically anonymized prior to data analysis by IMS.

### Assessments

As part of the eligibility procedure, delirium risk will be assessed using a validated five-item delirium risk screening tool (see “Is the resident at risk?” section of the Decision Tree, Fig. 2) [36]. To be included for study, a resident will require a score of 1 or higher on this scale. Prevalence of delirium will be then assessed weekly for 2 weeks at baseline (screening), and only residents with two consecutive negative CAM scores will be considered for trial inclusion. Delirium incidence and severity (primary outcomes) will be assessed weekly during the 18-week follow-up period. These delirium assessments will be completed using the CAM [37, 38] and the DI [39] as part of a standardized interaction with the resident based on a series of questions adapted using items from various cognitive assessment tools, specifically the Mini-COG (memory) [51–53], Montreal Cognitive Assessment (orientation) and Hierarchical Dementia Scale (concentration) [36, 40, 51, 54, 55]. Functional autonomy will be evaluated at the beginning and end of the follow-up period (weeks 1 and 18) using the Shah version of the Barthel Index [56], an ordinal scale used to measure independence in the activities of daily living (ADLs) adapted to the LTCF environment. Cognitive function will be also be evaluated at these time points using the Hierarchic Dementia Scale (HDS) [55]. Resident comorbidity will be assessed via chart review and reported using the Charlson Comorbidity Index [57] and Geriatric Comorbidity Index [58]. Resident frailty will be assessed via a combination of comorbidity and other measures of well-being, such as functional autonomy, social engagement, and healthcare utilization [59]. Medication information and anticholinergic drug use will also be extracted from resident medical charts, and assessed using the Anticholinergic Burden Scale [60]. Fig. 4 presents a visual representation of the enrolment, intervention, and assessment schedule (SPIRIT Diagram).

**Fig. 4 Fig4:**
[figure not shown]
PREPARED Trial SPIRIT Diagram

### Statistical data analysis

All statistical analyses will be conducted using SAS version 9.4, STATA version 13.0, and R software. Our study has four primary objectives, four secondary, and six tertiary objectives, all aimed at comparing the effect of our PREPARED Trial intervention to that of usual care. Data analysis will be conducted and reported in accordance with current CONSORT guidelines [61, 62].

For each outcome, we will report the estimates of the regression coefficients obtained from the model for the intervention: Hazard Ratio for survival analysis, beta estimate for the continuous outcome, Incident Rate Ratio for the count outcome, and Odds Ratio for the binary outcome. We will also report the ICC (ratio of the variance explained by the LTCF to the total variance explained by the model). All analyses will be conducted at alpha 0.05 and 95% confidence intervals will be reported.

Missing or incomplete outcome data will inevitably appear in our study. Our general approach will be based on intention-to-treat, using inverse probability weighting to account for missing data [63, 64]. To assess the appropriateness of this approach to missing data, we will conduct two sensitivity analyses using the following approaches: 1) inclusion of subjects with complete data only; and 2) use of multiple imputation for missing data [65, 66].

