**Methods:**

The objective is to assess the effectiveness of the multicomponent PREPARED Trial intervention in reducing the following primary outcomes: incidence, severity, duration, and frequency of delirium episodes in cognitively impaired residents. This 4-year, parallel-design, cluster randomized study will involve nursing staff and residents in 45–50 LTCFs in Montreal, Canada. Participating public and private LTCFs (clusters) that provide 24-h nursing care will be assigned to either the PREPARED Trial intervention or the control (usual care) arm of the study using a covariate constrained randomization procedure. Approximately 400–600 LTC residents aged 65 and older with dementia and/or cognitive impairment will be enrolled in the study and followed for 18 weeks. Residents must be at risk of delirium, delirium-free at baseline and have resided at the facility for at least 2 weeks. Residents who are unable to communicate verbally, have a history of specific psychiatric conditions, or are receiving end-of-life care will be excluded. The PREPARED Trial intervention consists of four main components: a decision tree, an instruction manual, a training package, and a toolkit. Primary study outcomes will be assessed weekly. Functional autonomy and cognitive levels will be assessed at the beginning and end of follow-up, while information pertaining to modifiable delirium risk factors, medical consultations, and facility transfers will be collected retrospectively for the duration of the follow-up period. Primary outcomes will be reported at the level of intervention assignment. All researchers analyzing the data will be blinded to group allocation.

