### Sample size calculation

Based on sample size calculations, we plan to recruit between 400 and 600 LTC residents in the current study. Sample size was computed for our primary objective, to detect any differences between our intervention and control trial arms in the incidence of a first delirium episode after 18 weeks of follow-up. We used the Freedman log-rank test method to compare two survivor functions at the end of study follow-up. In a post-hoc secondary analysis of the precursor LTC delirium study, for which we applied the PREPARED Trial inclusion and exclusion criteria [33], we obtained incidence rates that we assume will be experienced by our control group, namely 3.75 cases per 100 person-weeks. We tested different scenarios concerning the size of our sample after 18 weeks of follow-up from baseline. We also tested our assumptions regarding the magnitude of our intervention effect by allowing the reduction in incidence rates to vary between 30 and 73%, as previous studies (in non-LTC settings) have reported this range in variation [1, 18–22]. Using methods of estimation ‘uncorrected’ for cluster randomization, we found that including 180 residents per trial arm (after assuming a 15% rate of attrition over our 18 week follow-up period to account for deaths, transfers and drop-outs) will enable us to detect a 40% reduction in the incidence of delirium (HR = 0.6) with a power of 80% at the 5% level (assuming 2-tailed test and equal group size).

The ‘corrected’ sample size for cluster randomization was then computed according to Rutterford et al. (2015) [42], where a design effect was incorporated that inflated the preliminary uncorrected calculation [43]. This design effect depends on two variables: 1) the Intra-cluster Correlation Coefficient (ICC) and 2) the number of clusters, where the total estimated required sample size is directly proportional to the magnitude of ICC and inversely proportional to the total number of clusters participating in the trial. Our sample size analysis, therefore, provides estimates using two conservative values for our expected outcome, and incorporates scenarios for both ICC and the number of clusters (or LTC facilities) that will be included in the study (Fig. 3).

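### Four outcomes are called primary and each is tested at 0.05 with no order or success rule, while the trial is sized for only one of them, first-episode incidence

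*Protocol article*

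**What the plan says.** The Abstract (Methods) names as primary the "incidence, severity, duration, and frequency of delirium episodes in cognitively impaired residents". Study objectives speaks of one primary objective but lists the same four effects under it. Statistical data analysis counts them separately: "Our study has four primary objectives, four secondary, and six tertiary objectives". The same section gives the only error rule in the article: "All analyses will be conducted at alpha 0.05 and 95% confidence intervals will be reported".

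Two other sections describe the primary outcome differently.

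- **Sample size calculation** uses the singular, "Sample size was computed for our primary objective", and defines it as a difference between arms in "control trial arms in the incidence of a first delirium episode after 18 weeks of follow-up". It adds: "We used the Freedman log-rank test method to compare two survivor functions at the end of study follow-up".
- **Assessments** attaches the primary label to incidence and severity only, when describing the weekly visits.

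No section gives a hierarchy, a gatekeeping order, an adjusted level or a definition of trial success. No section gives power for severity, duration or number of episodes.

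**The concern.** With four primary outcomes, the planned 5% error level describes the trial's main conclusion only if the plan says how the four results combine. Under this text, a trial that missed on incidence but reached p<0.05 on duration, for example, could be reported as positive on a primary outcome. The Discussion expects the results to feed into clinical guidelines and speaks of prevention across all four outcomes, so the gap bears on the main claim.

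This goes beyond detail that an article leaves to an analysis plan. The article itself fixes the number of primary outcomes and the level for each, and its own sections disagree on which outcomes are primary.

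**Working it through.** **1. Which outcome the stated sample size serves.** Inputs from Sample size calculation: control rate 3.75 per 100 person-weeks, 18 weeks, HR 0.6, 80% power, two-sided 5%, 15% attrition, equal arms.

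- Freedman events: ((1+0.6)/(1−0.6))² × (1.960+0.842)² = 16 × 7.849 = 125.6, so 126.
- Event-free at 18 weeks: control exp(−0.0375×18) = 0.509; intervention 0.509^0.6 = 0.667; mean 0.588.
- Evaluable: 126/(1−0.588) ≈ 306 in total, 153 per arm.
- With attrition: 153/0.85 = 180 per arm.

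This reproduces the article's 180 per arm before cluster correction. The trial was therefore sized for one outcome at the full 0.05, with nothing set aside for three more primary tests.

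**2. Any one of four succeeds.** With all four null hypotheses true and independent tests, 1 − 0.95⁴ = 0.185. The article gives no correlations, so the other rows assume equal pairwise correlation. They come from simulating four standard normal test statistics, 2 million draws per row. Benefit only counts significant results favouring the intervention, against a nominal 2.5%.

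| Assumed correlation | Either direction | Benefit only |
|---|---|---|
| 0 | 18.5% | 9.6% |
| 0.3 | 17.4% | 8.8% |
| 0.5 | 15.6% | 7.8% |
| 0.7 | 13.0% | 6.5% |
| 0.8 | 11.4% | 5.7% |
| 0.9 | 9.4% | 4.7% |

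If only the two outcomes labelled in Assessments were primary, the independent figure would be 1 − 0.95² = 9.75%.

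**3. All four must succeed.** The chance of four false positives cannot exceed 5%, so nothing is inflated. Joint power cannot exceed that of the weakest test, so it is at most the 80% planned for incidence. How far below 80% it lies cannot be worked out, because the other three have no stated power.

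**4. What the repairs cost.**

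- Bonferroni, 0.05/4 = 0.0125 each: with 126 events, power for incidence is Φ(√126 × 0.25 − 2.498) = Φ(0.31) ≈ 62%. Restoring 80% takes 16 × (2.498+0.842)² ≈ 178.4, so 179 events, or about 218 evaluable and 256 enrolled per arm. All of these are before cluster correction and compare with 180 per arm. They show the relative cost of splitting alpha and are not the power of the trial as enrolled.
- A single primary outcome, or a fixed sequence that starts with incidence: incidence keeps 0.05, so 126 events and 180 per arm stand.

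**The case against.** The strongest reply is that the article never says one success out of four is enough. Study objectives can be read as four specific aims under one objective. If each claim is confined to its own outcome, each test keeps its 5% level. The Discussion's wording, which joins all four outcomes, fits an all-must-succeed reading at least as well. This stands. A reader might infer that the trial carries an 11–18% chance of a false primary claim. The documents do not support that as a fact: it needs both an any-one rule that is written nowhere and correlations that are given nowhere.

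Three further points have force.

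- **Independence is implausible for at least one pair.** A resident with no first episode has an episode count of zero. Simulating weekly onset at the article's control rate, with 153 residents per arm and no clustering, gives a correlation of about 0.89 between the log-rank and episode-count statistics. If the other two tests were independent of these and of each other, the familywise error would be about 16%, so 18.5% is an upper end.
- **The larger figures count both directions.** For false claims of benefit the range is roughly 6–10% at correlations of 0.8 to 0, against 2.5%.
- **Testing at 0.05 does not exclude an order.** A fixed sequence also tests each outcome at 0.05, and an analysis plan not shown here may contain one. Sizing a trial on one lead outcome is also ordinary practice.

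These limit the size of the point without removing it. The sections still disagree on what is primary, and every outcome called primary is given the full level with no rule for combining them.

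**Conclusion.** The point holds as an internal inconsistency with a conditional consequence. The Abstract, Study objectives and Statistical data analysis give primary status to four outcomes, Sample size calculation powers one, and Assessments labels two. The success rule is not stated.

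If any one significant primary counts as success, the two-sided familywise error exceeds 5% at every correlation examined, from 18.5% at 0 to 9.4% at 0.9. These figures assume all four null hypotheses are true and, apart from the first, equal pairwise correlations chosen for illustration. If all four must succeed, the error is controlled, but the planned 80% is then a ceiling and the actual power is unknown. The stated combination of 80% power and a 5% level describes a trial with first-episode incidence as its sole primary outcome, which the other sections do not describe.

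**What to change.** Before the analysts see allocation:

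- Name time to first delirium episode over 18 weeks as the single primary outcome, tested at two-sided 0.05, in line with Sample size calculation.
- Make severity, duration and number of episodes key secondary outcomes, tested in a prespecified fixed sequence at two-sided 0.05, with formal claims stopping at the first non-significant result. The order is the sponsor's choice; the article gives no basis for preferring one.
- Align the Abstract, Study objectives, Assessments and Statistical data analysis with this. The sentence on alpha can stay if the sequence and stopping rule are added beside it.

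The cost is wording, in the protocol and wherever the analysis plan and registration repeat the list of primary outcomes. The real downside is that three outcomes lose stand-alone primary status, and a non-significant incidence result would end formal claims for them. Data collection, sample size and power for incidence do not change.
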